### Outcome Measures

Each participant will attend six assessment days in total as follows: baseline (week 0) and week 3, week 5, week 8, week 16, and week 24 posttreatment sessions. At each assessment day, three assessments will be given to the participant in the following fixed sequence: ADAS-Cog, verbal fluency test, and Stroop test. Only the patient and the research personnel designated to administer assessments will be in the room during assessments. At the baseline and week 5 and week 16 posttreatment assessments, additional caregiver assessments will be performed. Alzheimer Disease Co-operative Study-Activities of Daily Living Inventory (ADCS-ADL) and Neuropsychiatric Inventory Questionnaire (NPI-Q) assessments will be performed at each of these visits (in that order), while the Treatment Satisfaction Questionnaire for Medication (TSQM) will only be used at the week 5 assessment. These outcome measures must be administered to the same caregiver at each visit. If a participant is accompanied to an assessment visit by someone other than their usual caregiver, the assessor will contact the usual caregiver by phone to complete these assessments.

All assessments will be performed on a Monday or the first working day of the week. Note that the specific dates of the last three assessments (the follow-up assessments) will be adjusted based on whether the participant is in a 2-week or 4-week treatment group. An assessor will be assigned to each participant. That same assessor must perform all of the six assessments with the assigned participant. Deviations should be justified (changes in staff, assessor illness, etc), and an explanation will be documented in the assessment notes.

As participant schedules are often busy, we can adjust the specific dates of the assessments within ranges (Table 1). If no assessment is possible within these windows, the assessment will be skipped and the data point will be missing from the analysis (with the exception of the baseline assessment, which will require rescheduling the treatment).

The primary outcome measure will be the change in patient scores from baseline on the ADAS-Cog assessment, as that is the most common standard test used in dementia clinical trials. Alternate forms of the ADAS-Cog word lists will be used at each visit to avoid possible practice effects. The secondary outcome measures will be the change in the scores from baseline of the proximal measures Stroop test [53] and verbal fluency test, as well as the distal measures NPI-Q and ADCS-ADL. We will also assess the tolerability of the rTMS treatment by the TSQM [54], which will be completed by patients and their primary caregivers posttreatment.

At each site, the above assessments will be administered by a study research assistant (RA) blinded to the group assignment of the patients. The RAs involved in administering treatment or assessments will not be involved in any of the statistical data analyses.

**Table 1 table1:** Date adjustments for assessments.

Assessment	Range of possible dates
Baseline	Up to 1 week before the first treatment
Week 3	+/− 1 day of the ideal date
Week 5	+/− 1 week of the ideal date, but after the final treatment
Week 8	+/− 1 week of the ideal date
Week 16	+/− 2 weeks of the ideal date
Week 24	+/− 2 weeks of the ideal date

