### Treatment Protocol

Patients in both the active and sham treatment groups will undergo daily (5 days/week) rTMS treatment. Each treatment will apply 25 trains of rTMS pulses bilaterally to the DLPFC. Each train will have a duration of 1.5 s, and pulses will be applied at 20 Hz (for a total of 30 pulses per train). The intertrain interval will be 10 seconds. Thus, there will be a total of 1500 pulses delivered to the brain per day (25×30=750 per side), resulting in a total of 30,000 pulses applied over the course of 4 weeks of treatment (20 sessions) or 15,000 pulses for 2 weeks of treatment (10 sessions). Each TMS treatment session will take approximately 10 to 25 minutes. Any missed treatment sessions will be made up on the following day, with a minimum 30-minute break between sessions.

The pulses will be applied at 90% to 100% of the RMT of each participant. The RMT, which will be measured for each hemisphere before the first treatment, is determined by applying single TMS pulses over the primary motor cortex and observing the lowest intensity at which it causes an involuntary twitch of the participant’s contralateral thumb. The specific process involves setting the intensity of the stimulator at 65% to 75% of the maximum intensity and adjusting the coil location over the primary motor cortex until the “hotspot” for activating the involuntary twitch is found. Then, the intensity is lowered in 1% decrements to find the lowest intensity at which an involuntary twitch can be clearly observed in three consecutive pulses. The intensity of treatment will be 90% to 100% of the RMT, unless the participant is having trouble tolerating the treatment, in which case treatment at an intensity of 90% of the RMT will be used for the first session and increased to the full dose of 100% by the end of the first week of treatment.

The location of the DLPFC will be determined using the BrainSight 2 navigation system [52] for TMS. The right and left DPLFCs of each participant will be localized using their own MRI scan, and the coil location and direction will be specified using the BrainSight software at Talairach coordinates (x, y, z) = (–50, 30, 36). The coil will be held at approximately 45 degrees relative to the horizontal axis, but this will be measured approximately rather than specified exactly using the neuronavigation software.

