To prevent unblinding, a Magstim sham coil will be used for sham treatments. This coil provides the same sound and tactile sensory experience as the real coil, but it attenuates the strength of the induced electrical field in the brain well below the threshold required to stimulate neurons. In addition, during treatment, only the participant and the research personnel designated to administer the rTMS will be present (no caregiver).

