### Safety Considerations

Before enrolling in the study, all participants will be screened for possible rTMS contraindications (seizure history, brain lesions, metallic implants, etc). Participants will be asked at each visit if they have experienced any adverse effects from the treatment. Any reported adverse events or effects will be recorded, and treatment will be suspended at the discretion of the study physicians if the adverse effect is considered to be serious (ie, life threatening or requiring hospitalization or medical treatment). The participant’s self-assessment of any pain or discomfort from the treatment will also be recorded at every visit.

A data and safety monitor board (DSMB) will oversee the study to ensure that proper safety procedures are followed and that adverse effects of the treatment are properly documented. If adverse effects are discovered that warrant a review or investigation before proceeding with the study, the DSMB will have the authority to initiate such a review. The DSMB will also ensure that the study does not deviate from the intended protocol.

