## Results

### Recruitment and Enrollment

As of November 1, 2020, we have screened 523 individuals, out of which 133 were eligible and have been enrolled. Out of the 133 individuals enrolled and randomized to the intervention groups, 104 have completed the study and 20 have discontinued the study or have withdrawn for various reasons at various stages of the study. Data of some withdrawn individuals who completed the study up to week 8 or 16 are still usable for analysis. Three individuals withdrew because they found the treatment uncomfortable, nine withdrew with no reason given, and eight were withdrawn by the site PI. Out of the eight withdrawn by the site PI, two were withdrawn for safety reasons as they developed some illnesses, although they were not related to the rTMS treatment, four were noncompliant (changed their medication during the study) or found the rTMS pulses unbearable, and two could not finish the treatment due to pandemic lockdown.

Recruitment and enrollment have been slower than initially anticipated, and the pandemic has slowed these even further. Before the pandemic, the realistic recruitment rate was one per month.

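### Tolerability rests on a single week-5 TSQM, which leaves out anyone who has left the study by then and may follow the last session by different intervals in the 2-week and 4-week groups

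*Protocol article*

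**What the plan says.** The Abstract (Methods) gives tolerability to a modified TSQM, and the Outcome Measures section repeats the assignment: "We will also assess the tolerability of the rTMS treatment by the TSQM [54], which will be completed by patients and their primary caregivers posttreatment". Earlier in the same section the form is listed with the additional caregiver assessments and limited to one visit: "while the Treatment Satisfaction Questionnaire for Medication (TSQM) will only be used at the week 5 assessment".

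On visit timing, Outcome Measures states: "the specific dates of the last three assessments (the follow-up assessments) will be adjusted based on whether the participant is in a 2-week or 4-week" arm. Those are weeks 8, 16 and 24, so week 5 is not among them. Table 1 allows week 5 a window of one week either side, provided that it comes after the final treatment. The Abstract, by contrast, counts all the follow-up visits in weeks after the intervention.

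On missing data, a visit that cannot be held in its window is skipped and its data point is missing (Outcome Measures). Last observation carried forward covers missing data and early termination (Analysis of the Results).

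Safety Considerations sets up two further records: "Participants will be asked at each visit if they have experienced any adverse effects from the treatment", and "The participant’s self-assessment of any pain or discomfort from the treatment will also be recorded at every visit".

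Recruitment and Enrollment reports on those who left. The entry that bears most directly on this point is "Three individuals withdrew because they found the treatment uncomfortable".

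**The concern.** Leaving because the pulses hurt is itself a tolerability outcome. A questionnaire given once, after treatment has ended, reaches only those still attending. If the TSQM alone carries the tolerability conclusion, the measure is selected on the thing it is meant to measure. The Abstract (Results) already anticipates that the treatment will prove well tolerated, so the omission matters for a conclusion that the authors expect to draw.

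Timing is a second issue. Patients enter with MoCA scores of 7 to 25 (Recruitment), so the interval over which they must recall the sessions is not a trivial detail. If that interval differs between the two durations, a comparison of their TSQM scores mixes treatment duration with time since the last session.

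Third, the section gives two accounts of the respondent. One paragraph places the TSQM among assessments made with the caregiver; a later one has both patient and caregiver complete it.

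**Working it through.** The plan states no figure for tolerability, so there is none to reproduce. Three checks apply.

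**1. Who can have a TSQM value.** There is one administration, at week 5. A patient who has left the study by then has no value. Carrying forward needs an earlier observation of the same instrument, and none is scheduled. The TSQM is therefore available only for week-5 attenders.

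**2. How many left for discomfort** (Recruitment and Enrollment, to November 1, 2020).
- Enrolled 133; completed 104; discontinued or withdrawn 20; neither, 133 − 104 − 20 = 9.
- The 20 are made up of 3 for discomfort, 9 with no reason given and 8 withdrawn by the site investigator. The 8 are 2 for unrelated illness, 4 who were noncompliant or found the pulses unbearable, and 2 because of lockdown.
- Certain: 3/133 = 2.3% of those enrolled, or 3/20 = 15% of the discontinuations.
- Upper limit on stated reasons, counting all four in the mixed category: (3 + 4)/133 = 7/133 = 5.3%, or 7/20 = 35% of the discontinuations.
- The nine with no reason given cannot be classified. The dates of leaving are not reported, so the number who left before week 5 is unknown.

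**3. Interval from last session to the TSQM.** Assumptions: the first session is on the Monday of week 1 (day 1), there are five sessions a week with none displaced, and the visit is on the Monday of week 5.
- Week-5 Monday: 7 × 4 + 1 = day 29.
- Last Friday session: 7 × (2 − 1) + 5 = day 12 for 2 weeks; 7 × (4 − 1) + 5 = day 26 for 4 weeks.
- Interval: 29 − 12 = 17 days against 29 − 26 = 3 days, a difference of 14 days.
- With the Table 1 window (days 22 to 36, and after the last session): 10 to 24 days for 2 weeks and 1 to 10 days for 4 weeks.

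This clock runs from the start of treatment, which two features of the text support. Re-dating only the last three visits by duration implies that weeks 3 and 5 share one calendar. And the Table 1 condition that week 5 follow the final treatment would be redundant if the weeks were counted from the end of treatment. If the Abstract's wording is taken literally, however, the interval is 5 weeks in both groups and the difference is zero.

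**The case against.** A reader might infer that patients who stop because of pain are never scored for tolerability. The documents do not support that. Safety Considerations records adverse effects and self-rated pain or discomfort at every visit and does not restrict this to completers, and the article itself reports the discomfort withdrawals. Nor does stopping treatment amount to missing week 5: withdrawals occurred at various stages, and some withdrawn patients have usable data to week 8 or 16. Whether a TSQM is collected at early termination is a detail that an article may leave to the full protocol. All of this stands, and it limits the point to the TSQM. It does not remove it, because the article gives the tolerability role to the TSQM and nowhere to the visit ratings.

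A reader might also infer that the unequal interval flatters one duration. Nothing in the documents establishes a direction. No numbered hypothesis concerns tolerability, and sham is also given for 2 or 4 weeks (Randomization), so active versus sham is affected only if the mix of durations differs between them. Nor can the bias in the TSQM result be sized: the article defines no category of poor tolerability on it.

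Two further inferences are weak. Caregivers are kept out of the sessions, but they can still see or be told of later headache or pain. And an assessor who hears of discomfort need not learn the allocation, since the sham coil is described as giving the same sound and touch; adverse effects are asked about at each visit in any case.

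**Conclusion.** The point holds in a limited form. The instrument named for tolerability is given once and covers only those who attend week 5; carrying forward cannot fill the gap. On stated reasons, 3 to 7 of 133 patients (2.3% to 5.3%) left for discomfort by November 1, 2020. This bounds the patients potentially affected to that date among those with a stated reason. It is not an estimate of how many lack a TSQM, because their dates of leaving are not given.

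The contrast of 17 and 3 days since the last session rests on a clock from treatment start and on sessions running to schedule; it disappears under the Abstract's wording. The inconsistency needs resolving whichever reading is meant. The primary outcome is not touched. What is at stake is whether a statement that rTMS was well tolerated can rest on the TSQM alone, and it cannot.

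**What to change.** - Define tolerability by arm in all randomised patients, as (a) the proportion stopping for pain or discomfort, counted separately from withdrawals for medication change, and (b) the pain and discomfort self-ratings already recorded at every visit. The four patients in the mixed withdrawal category need to be split by reason.
- Keep the week-5 TSQM as a supportive satisfaction measure, labelled as covering week-5 attenders only, and do not use it alone to claim that treatment was well tolerated.
- Reconcile the Abstract with Outcome Measures and Table 1 on where the week count starts. If it starts with treatment, note the unequal recall interval in any 2-week versus 4-week comparison of TSQM scores.
- Reconcile the two paragraphs of Outcome Measures on whether the patient, the caregiver or both complete the form.

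The cost is wording, a little more analysis and possibly a less favourable tolerability figure; no new data collection is needed. Moving the TSQM to the last session is not recommended here. It would split the dataset after 104 completions, and it would place a subjective form in a session where the only staff present are those giving the rTMS, and the rTMS administrator knows the allocation.

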### Adverse Events

We have developed a series of detailed questions to mark any plausible adverse effect of the treatment, and the series is used consistently among the different sites of the study. As of November 1, 2020, there has been no serious adverse event. However, 89 of the participants reported expected adverse events as described in the Plausible Side Effects section above. Twelve participants reported some unexpected adverse events, which were most likely unrelated to the rTMS treatment. The reported events were increased blood pressure on one day, a nightmare, vivid dreaming, sleeping trouble, disorientation, blurry vision, and unsteadiness on the feet for a few minutes. All reported cases were temporary and reported on only one day. All issues resolved without medication. All adverse events have been described in detail in quarterly DSMB reports.

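### The blinded assessor who rates cognition at all six visits also administers the week-5 tolerability questionnaire, an avoidable unblinding risk to the ratings at weeks 8, 16 and 24

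*Protocol article*

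**What the plan says.** Outcome Measures sets six assessment days (baseline and weeks 3, 5, 8, 16 and 24), with ADAS-Cog, verbal fluency and Stroop in that order on each. It ties one rater to each participant: "That same assessor must perform all of the six assessments with the assigned participant". Departures need a documented reason.

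The TSQM is listed with the caregiver instruments: "the Treatment Satisfaction Questionnaire for Medication (TSQM) will only be used at the week 5 assessment". If someone other than the usual caregiver attends, "the assessor will contact the usual caregiver by phone to complete these assessments". Its purpose is stated in the same section: "We will also assess the tolerability of the rTMS treatment by the TSQM", "which will be completed by patients and their primary caregivers posttreatment". The next paragraph says that "the above assessments will be administered by a study research assistant (RA) blinded to the group assignment of the patients".

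Safety Considerations adds: "Participants will be asked at each visit if they have experienced any adverse effects from the treatment". It also has pain or discomfort recorded at every visit. It names no role for either task.

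Experimental Design commits assessors to blindness on both treatment type and length of course.

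**The concern.** ADAS-Cog and the two secondary cognitive tests are administered and scored by a person, so they depend on that person not knowing the arm. As written, the plan passes information about how the treatment was experienced through that same person, partway through the series of ratings.

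The article gives reasons to think such information could matter. Plausible Side Effects attributes headache and scalp, eye and neck pain to rTMS. Recruitment and Enrollment records withdrawals because the stimulation was uncomfortable. The Treatment Protocol keeps caregivers out of treatment sessions, while the week-5 questionnaire then asks patients and caregivers about tolerability through the rater.

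What is at stake is the longer-term comparison of active with sham treatment, up to six months, which the Abstract states as an aim. The visits after week 5 supply that evidence.

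**Working it through.** The point is procedural. The check sets the statements side by side.

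1. **Who rates cognition.** One assigned assessor at all six visits (Outcome Measures).

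2. **Who gives the TSQM.** It is a week-5 instrument in the caregiver set. The assessor completes that set with the usual caregiver, by phone if needed. The TSQM is also named in the paragraph just before the sentence assigning the preceding assessments to the blinded research assistant. The article names nobody else for it. The cognitive rater and the person administering the TSQM are therefore the same.

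3. **Which ratings follow it.** There are 6 − 1 = 5 post-baseline visits. Weeks 8, 16 and 24 come after the TSQM, so 3 of 5. The week-5 ratings could be reached only if the TSQM preceded them that day. Its place relative to the cognitive tests is not stated.

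4. **Side-effect and pain questions.** Safety Considerations is in the passive voice and does not say whether a visit means a treatment visit, an assessment visit or both. If assessment visits are included, Outcome Measures admits only the patient and assessing staff to the room during assessments, so the rater asking is a reasonable reading, but it is not stated. Nothing says the answers are withheld from the rater.

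5. **Against the blinding commitment.** Experimental Design promises blindness to type and duration. Steps 2 to 4 leave a route by which treatment experience can reach the rater, and no barrier is described.

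6. **How informative the route is.** Adverse Events reports that "89 of the participants reported expected adverse events". Taking all 133 enrolled as the denominator (an assumption, since the article does not state it), 89/133 = 0.669. This is a weighted mean of the active and sham rates. Equal rates of 66.9% in both satisfy it, in which case side-effect reports carry no information about the arm. So do unequal rates, in which case they carry some. The pooled count cannot tell these apart.

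**The case against.** Four points are fairly made on the other side.

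- **The collector of side-effect and pain reports is not named.** A reader might infer that the assessor takes them. The documents do not say so. The wording sits beside the rule on suspending treatment, so daily treatment visits with the rTMS administrator are just as natural a reading. A journal article that leaves out the collector is condensing, and that silence alone is no error. This stands. The point rests on the TSQM, which the article does assign, and the safety questions enter only because no separation from the rater is stated.

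- **The sham may make the answers uninformative.** The Treatment Protocol says the sham coil reproduces the noise and feel of the real one. A reader might take tolerability answers to be arm-revealing, or turn the 67% into a rate of correct guesses. Without rates by arm, any such figure would rest on invented inputs. This stands too.

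- **The form is completed by patients and caregivers.** Whether the rater sees the answers is not explicit. That weakens the point for a paper form but hardly for completion by phone, where the assessor would ordinarily hear the replies.

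- **Scoring is cross-checked.** Quality Assurance has assessors at another site check scoring and data entry. This limits errors in scoring. It cannot remove differences in how a test was administered in the room.

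None of these explains why the cognitive rater needs to handle the tolerability form.

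**Conclusion.** The point holds as an avoidable unblinding risk created by the stated procedure. The cognitive rater administers the week-5 tolerability questionnaire ahead of three of the five post-baseline ratings, and no barrier is described for side-effect and pain answers at assessment visits. It is a cheap improvement and does not show that blinding failed. The size of any bias is unknown and could be zero.

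Three further inferences are tempting and should not be drawn:

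- **That the test of H3 is biased as an active-sham contrast.** Study Goal, Objectives, and Hypotheses defines H3 as duration of effect among responders to active treatment. The exposure is to the longer-term active-sham comparison in the Abstract.
- **That the primary pre-post comparison is compromised.** The TSQM comes only at week 5, and its order relative to that day's ADAS-Cog is not given.
- **That TSQM results are distorted between 2-week and 4-week courses by unequal recall.** The article plans no such comparison.

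The conclusion assumes that the sentence assigning the preceding assessments to the blinded research assistant includes the TSQM. The text supports this directly.

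**What to change.** Amend Outcome Measures and Safety Considerations to say that:

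- the TSQM is given after that day's cognitive ratings, either as a self-completed form returned sealed or taken by existing staff who do not rate that participant, and that this covers any completion by phone;
- any side-effect and pain questions at assessment visits are asked by existing non-rating staff, and the answers are withheld from the rater;
- participants and caregivers are asked not to discuss treatment experience with the assessor.

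Two alternatives are less suitable. Having the unblinded rTMS administrator run the TSQM could influence the answers, and caregivers do not attend treatment sessions. Relying only on self-completed side-effect sheets could weaken safety capture in participants with MoCA scores as low as 7.

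The cost is protocol wording and minor logistics, mostly at the week-5 visit. No new instrument is needed, and side-effect questions are still asked in person. At the article's count, 133 − 104 − 20 = 9 participants were still in progress. The change can help them and later enrollees, but not those who had finished. For the latter, the trial report should state who took the TSQM and the side-effect reports.
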